### Concealment mechanism {16b}

The Institute of Epidemiology and Medical Biometry at Ulm University will carry out the randomisation, guaranteeing the independence of the group allocation from the data collection and analysis processes.

All participants who give consent to participation and fulfil the inclusion criteria will be randomised. For this, GBV teams will contact the local research worker who will schedule the baseline assessment (*t*_0_) and request randomisation by e-mail from the Institute of Epidemiology and  Medical Biometry, Ulm University, Germany. The randomisation form includes the participant ID (including his/her study ID), date of informed consent, and approval of eligibility. The requesting research worker will obtain a response by mail within one working day. Allocation disclosure will occur after the baseline assessment is completed, with the attendance of the participant, the research worker, and a member of the GBV team.

### Implementation {16c}

The Institute of Epidemiology and Medical Biometry at Ulm University will generate the allocation sequence. The GBV teams will enrol participants and inform the research workers at Ulm University about the participants’ enrolment. The research workers will initiate randomisation, collect baseline data, and assign the participants to interventions.

## Assignment of interventions: blinding

### Who will be blinded {17a}

Due to the type of intervention, blinding of the participants and service providers is not feasible. Furthermore, research workers responsible for data collection cannot be blinded, since they would have been unblinded at the latest when documenting GBV-specific services in the CSSRI and when collecting the data for process evaluation. The same applies for all researchers involved in data monitoring and data management. Thus, only the researcher performing the main analysis will be blinded until analysis has been completed.

### Procedure for unblinding if needed {17b}

Group affiliation of study participants will be revealed to the statistician by the data manager on duty after the finalisation of the main data analysis.

## Data collection and management

### Plans for assessment and collection of outcomes {18a}

Screening will take place at local mental health care facilities, and GBV team members will collect the data in paper-based form. The local research worker will collect further data (from *t*_0_ to *t*_4_) at a location of the study participant’s choosing, primarily in electronic form. If electronic data collection is not possible, the data will be collected on paper and electronically transferred later. Informal caregivers will be asked to fill out paper-based questionnaires on their own and send them by mail to the coordinating centre. Centralised electronic data capture is intended for these questionnaires. If necessary, specific issues will be clarified by phone.

Study-specific questionnaires will be compiled for sociodemographic data, medical history, living conditions, and social life. At the follow-up assessments (*t*_1_, *t*_2_, *t*_3_, and *t*_4_), a study-specific fidelity scale will be used to assess interventional compliance among the service providers and to gain ancillary information about the importance of and the satisfaction with local community mental health services from the patients’ perspective. In addition, all local GBV providers will be asked to answer a catalogue of quality criteria for community mental health care as defined on the basis of the  S3 guideline “Psychosocial Therapies for Severe Mental Illnesses” of the DGPPN [1] in order to check for adequate implementation of GBV. Standardised questionnaires will be used to assess further process variables such as interprofessional collaboration and recovery orientation.

Only standardised questionnaires with known and at least satisfactory psychometric characteristics will be used to assess the outcomes:
Assessment of Empowerment in Patients with Affective and Schizophrenic Disorders (EPAS) [14]Questionnaire of Treatment Satisfaction (ZUF8) [15, 16]World Health Organisation Quality of Life—short version (WHO-QoL-BREF) [17]Camberwell Assessment of Need—European version (CAN) [18, 19]Health of the Nation Outcome Scale (HoNOS) [20–23]Euro Quality of Life—5 dimensions (EQ-5D) [25]Client Sociodemographic and Service Receipt Inventory (CSSRI) [24]Involvement Evaluation Questionnaire (IEQ-EU) [26]

The primary outcome will be measured by means of the EPAS, which measures empowerment as the patient’s perceived possibilities to control his or her own life on five dimensions: daily living, social relationships and sexuality, psychiatric treatment, hope and self-efficacy and self-esteem. This self-assessment instrument has 33 items and five additional items each for patients who are employed and for patients with minor children. Cronbach’s *α* = 0.94 was obtained for the total scale [14]. Originally developed to assess empowerment in patients with affective and schizophrenic disorders, the EPAS has also proved to be reliable in patients with other types of severe mental disorders [10, 28].

The German short version of the Client Satisfaction Questionnaire (CSQ8), published as Fragebogen zur Patientenzufriedenheit (ZUF8) [15, 16], is a suitable tool for measuring patient satisfaction with their mental health care.

The WHO-QoL-BREF captures the patients’ subjective quality of life in the dimensions of physical health, mental well-being, social relationships, and environmental conditions. The WHO-QoL-BREF is a self-assessment tool with 25 items [17].

The CAN records patients’ perceived needs and the extent to which they are met, covering 23 areas. No special knowledge is required to work with this instrument [18, 19].

The HoNOS measures the clinical and psychosocial impairment of patients in twelve dimensions, independent of diagnosis. After an appropriate briefing, members of all mental health professions can carry out the HoNOS assessment [20–23].

The EQ-5D enables the assessment of health conditions as a basis for determining quality-adjusted life years (QALY) [25].

The use of health and psychosocial care services will be recorded using the CSSRI [24]. Health care costs are estimated by multiplying the service units used by the billing costs per unit for a 6-month period. For the health economic analysis from the perspective of statutory health insurance, expenditures will be determined on the basis of billing data.

The German version of the Involvement Evaluation Questionnaire (IEQ-EU) [11] will be used to assess the burden on informal caregivers.

To assess treatment satisfaction and subjective quality of life, the same instruments will be used for informal caregivers as for patients, specifically the ZUF8 [15, 16] and the WHO-QoL-BREF [17].

Dropouts and adverse events will be documented on standardised forms at the next follow-up assessment, at the latest.

Only trained GBV team members will administer the EPAS, CAN, and HoNOS and lead the enrolment procedure. A contact person at the coordinating centre will be available to GBV team members throughout the course of the study to answer questions on participant enrolment and screening. Refresher trainings will be offered as needed.

All local research workers have been trained and will follow uniform standard operating procedures (SOP) as to good clinical practice (GCP), recruitment, assessment, and questionnaires, for example. Advanced training sessions (e.g. training in HoNOS evaluation) of the research associates will be part of biannual project meetings. During the study, local research workers will be regularly tested for interrater reliability on the HoNOS and CAN using case vignettes.

Research workers at the coordinating centre will check the quality of data collection at each site during semiannual monitoring visits. The results will be documented in a monitoring report, which will be sent back to the local research workers and considered for the final analysis and interpretation of the data. The focus of the monitoring will primarily be on site monitoring, i.e. whether the local research workers are conducting the study in accordance with the given SOP. Furthermore, the monitoring will involve checking the completeness and plausibility of the available study documents. During the 1-year recruitment phase, the inclusion of study participants in accordance with the study protocol will be checked (e.g. by checking their eligibility and informed consent). Thereafter, the monitor will focus on the completeness and plausibility of the collected data and the documentation of serious adverse events. In addition, the monitor will offer support in case of questions or ambiguities in terms of participant recruitment, study conduct, and data collection and reporting, thus contributing to increased data quality.

### Plans to promote participant retention and complete follow-up {18b}

Participants will receive reimbursement for study participation (€25 per study visit, from *t*_0_ to *t*_4_) and, if applicable, for their expenses for travelling to the interview location.

### Data management {19}

Data will primarily be collected using the survey software SoSci Survey (SoSci Survey GmbH, Munich). The value ranges for the individual questions are defined in the electronic form of the questionnaire. A check for missing values is performed for each questionnaire in the electronic form. If not feasible, a paper version of the questionnaire will be used and transcribed into electronic format by the local research worker within 1 week. In order to check the data entry, staff at the coordinating centre in Ulm will re-enter a randomly chosen 5% sample of the paper-based data and subsequently compare the data sets.

All collected data will be regularly requested and stored on servers at the Department for Psychiatry and Psychotherapy II of Ulm University. Research workers at the coordinating centre at Ulm University will process and analyse the data. The data processing will include electronic data checks for plausibility and completeness as well as subsequent preparation for analysis. The data will be processed and evaluated with the software packages SPSS and SAS, among others.

The coordinating centre will oversee the whole study process by frequently communicating with local research workers regarding outstanding issues, checking the data collection procedure, and sending queries, if necessary.

### Confidentiality {27}

The collection, storage, and analysis of study data will be carried out in compliance with the relevant data-protection regulations. All personal data will be pseudonymised during the collection. The study participants’ personal identifying data will be replaced by identifiers. The index tables for the assignment of personal data and identifiers will be access-protected and stored separately from the data.

Communication and data transfer between the research team and both the local community mental health care providers and statutory health insurances will take place using screening identifiers. Local research workers will use study identifiers (different from screening identifiers) for data collection during the baseline and follow-up assessments (from *t*_0_ to *t*_4_). The local research workers will be the only persons with access to the major index table with personal data, screening identifiers, and study identifiers.

Prior to enrolment in the study, the potential study participants will be informed orally and in writing about the study’s aims, nature, scope, and implications by local GBV team members. In addition, the potential study participants will be informed about the data-protection regulations within the study. The potential study participants will be given sufficient time to think about their participation and to ask questions. By completing the informed consent form, the potential study participant will agree to participate in the study and to the data-protection regulations.

The study results will be published in anonymous form. This means that it will not be possible to allocate study data to individual study participants since no access to the index tables will be given.

The study data will only be transferred in anonymised form to third parties.

The study data will be archived on servers at the Department for Psychiatry and Psychotherapy II of Ulm University.

### Plans for collection, laboratory evaluation, and storage of biological specimens for genetic or molecular analysis in this trial/future use {33}

No biological specimens for genetic or molecular analysis will be collected in this trial.

## Statistical methods

### Statistical methods for primary and secondary outcomes {20a}

The data will be managed using IBM SPSS 25 and analysed using STATA 15 and SAS 9.4.

In order to evaluate the indication for GBV, the interrater reliability will be determined (using Spearman rank correlation) for the EPAS, HoNOS, and CAN ratings between screenings carried out by GBV team members and the baseline assessments carried out by local research workers. Furthermore, the criteria for serious mental illness will be assessed in the baseline data, and descriptive statistics will provide information on whether the target population has been recruited.

The analyses of primary and secondary outcomes will follow the intention-to-treat (ITT) principle using mixed-effects models with random time effects and time × treatment interaction effects. The covariance structure will take the study sites and individuals into account.

The cost-effectiveness ratios will be determined using the net benefit method, from the perspectives of both the statutory health insurance and national economy.

The implementation of GBV at the study sites will mainly be evaluated using descriptive methods. Mediator and moderator analysis will be conducted for the process variables, such as recovery orientation and multiprofessional collaboration.

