### Objectives {7}

The aims of this study are to examine the adequate implementation, effectiveness, and cost-effectiveness of the community-based mental health care programme GBV for people with severe mental illness in Germany.

The following hypotheses will be examined individually:
Community-based mental health institutions can integrate GBV into regular mental health care for people with severe mental illness.The indications for GBV can be assessed validly and reliably based on objective criteria.Compared to CAU, the use of GBV leads to a stronger empowerment effect, made apparent by an improved subjective ability to live a self-determined and self-reliant way of life, independently arrange social relationships, actively participate in mental health care, and have increased expectations of self-efficacy and future expectations (primary outcome criterion).Compared to CAU, the use of GBV leads to a stronger improvement of subjective quality of life as well as reductions to unmet care needs and the clinical and social impairment of patients related to their illness.Compared to CAU, the use of GBV leads to a greater reduction in the burden on informal caregivers and to improvements in their quality of life.From a health economic perspective, the use of GBV improves the cost-effectiveness ratio of the resources used, compared to CAU.From the perspective of the statutory health insurance, the implementation of GBV does not lead to a significant increase in expenditures.

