### Eligibility criteria {10}

The inclusion criteria for participants are as follows:
Minimum age: 18 yearsPresence of mental illness in ICD-10 diagnosis groups F2, F3, F4, F5, or F6Membership in a participating health insurance companyPermanent residence in one of the twelve defined project regionsIndications for GBV established by a screening assessment

Within a structured assessment, the local GBV teams will assess the indications for GBV in consultation with a physician or psychotherapist. The following standardised scales will be applied as part of the assessment:
The Assessment of Empowerment in Patients with Affective and Schizophrenic Disorders (EPAS), to determine the participants’ self-assessed ability to lead a self-determined and responsible way of life.The Camberwell Assessment of Need (CAN), to determine unmet needs, which is an external assessment by members of the GBV team.The Health of the Nation Outcome Scale (HoNOS), to determine patients’ clinical and social impairment due to illness, which is an external assessment by members of the GBV team.

The cut-off values for the three scales were derived from data from a previous study on integrated mental health care in Germany [10]. These cut-offs are ≤ 3.3 for mean EPAS total score, ≥ 4 for CAN unmet needs (sum score), and ≥ 12 for HoNOS total sum score.

Based on the results of these scales and upon consideration of the clinical evaluation in consultation with a physician or psychotherapist, the following decision regulations will be applied:
Within cut-off values for all scales: no indication for GBVOutside cut-off values for one or two scales: indication only with a clinical recommendationOutside cut-off values for all three scales: indication for GBV

The exclusion criteria for participants are as follows:
Primary clinical diagnosis in ICD-10 groups F0, F1, F7, F8, or F9Participation in other integrated mental health care programmes in the last 6 months before recruitment

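### Reliability of the GBV indication is judged by Spearman correlation alone, which a uniform rating shift across the absolute cut-offs does not change; for the self-rated EPAS the comparison is test-retest, not interrater

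*Protocol article*

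**What the plan says.** Objectives {7} lists as a hypothesis that "The indications for GBV can be assessed validly and reliably based on objective criteria".

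Eligibility criteria {10} sets the indication by fixed scores: "≤ 3.3 for mean EPAS total score, ≥ 4 for CAN unmet needs (sum score), and ≥ 12 for HoNOS total sum score". If no scale is beyond its cut-off, there is no indication. One or two scales beyond give an indication only with a clinical recommendation, and all three give an indication.

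Statistical methods {20a} gives the analysis. It opens with the purpose, "In order to evaluate the indication for GBV", and then says that "the interrater reliability will be determined (using Spearman rank correlation) for the EPAS, HoNOS, and CAN ratings". The two sets of scores compared are the GBV team's at screening and the research worker's at baseline. No other agreement statistic is named.

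On who rates what, Eligibility criteria {10} describes HoNOS as serving "to determine patients’ clinical and social impairment due to illness, which is an external assessment by members of the GBV team", and CAN is likewise an external rating by the team. EPAS serves "to determine the participants’ self-assessed ability to lead a self-determined and responsible way of life". Plans for assessment {18a} confirms this: "This self-assessment instrument has 33 items".

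**The concern.** The hypothesis concerns a decision made by comparing scores with fixed thresholds. The question is therefore whether two raters give the same score, or at least put the patient on the same side of the threshold. Spearman answers a different question: whether they order patients alike.

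The GBV teams that screen also deliver the programme, so a tendency to rate need upward is a plausible failure that this analysis should be able to detect. The protocol gives no evidence that it occurs. If it did, and were uniform, the planned statistic could report good reliability for an indication that does not reproduce.

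The EPAS problem is separate. The patient is the rater on both occasions, so the screening-to-baseline association cannot measure agreement between raters.

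**Working it through.** The protocol states no reliability coefficient or target for this analysis, so there is no figure to reproduce. The check asks how the named statistic behaves against the stated cut-offs.

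**Step 1: no assumptions beyond a constant shift.**
- HoNOS scores 4 to 24 from one rater, the same scores plus 3 from the other: Spearman = 1.000. Patients scoring 9, 10 or 11 move to 12, 13 or 14 and cross the cut-off of 12.
- CAN unmet needs 0 to 14, plus 2: Spearman = 1.000. Scores of 2 and 3 cross the cut-off of 4.

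**Step 2: size with rating error.** Assumed inputs, none from the protocol: HoNOS mean 13, SD 5, single-rating reliability 0.80, normal scores, unrestricted sample. Total variance is 25, true-score variance 0.80 × 25 = 20, error variance 5. The GBV team rates higher by a constant d.
- Spearman = (6/π) × arcsin(0.80/2) = 0.786 for every d.
- Absolute-agreement, single-rater ICC = 20 / (20 + 5 + d²/2), where d²/2 is the variance between the two raters.
- Share at or above 12 at screening = Φ((13 + d − 12)/5).

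| d | Spearman | ICC | Screening share ≥ 12 |
|---|---|---|---|
| 0 | 0.79 | 20/25 = 0.80 | Φ(0.2) = 58% |
| 2 | 0.79 | 20/27 = 0.74 | Φ(0.6) = 73% |
| 3 | 0.79 | 20/29.5 = 0.68 | Φ(0.8) = 79% |
| 4 | 0.79 | 20/33 = 0.61 | Φ(1.0) = 84% |

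The research-worker share stays at 58% throughout. At d = 3, kappa at the cut-off falls from 0.59 to 0.45.

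**Step 3: sensitivity to the assumed mean and SD.** Simulation with whole-number scores, 200,000 pairs, reliability 0.80; means 10, 12 and 14 with SD 5, and mean 12 with SD 6. At d = 3, Spearman is 0.78 in all four, as it is without over-rating. ICC is 0.67 to 0.71 (0.80 without over-rating) and kappa 0.43 to 0.49 (0.58 to 0.59 without).

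**Step 4: over-rating that differs between sites.** If the shift varies between sites with SD s, the screening variance becomes 25 + s² and the pooled correlation is 20/√(25 × (25 + s²)). For s = 2 this is 0.743, a Spearman of about 0.73. For s = 3 it is 0.686, about 0.67. A pooled Spearman would fall, but it would show neither the direction nor the size of the over-rating.

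**Step 5: other checks in the protocol.** The vignette tests in Plans for assessment {18a} cover research workers only. The baseline descriptives in Statistical methods {20a} concern criteria for serious mental illness. Monitoring checks eligibility, but no re-rating is described. None of these compares GBV-team with research-worker scores at the cut-offs.

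**The case against.** **The trial's main result is untouched.** Screening precedes randomisation stratified by site, so over-rating enters both arms alike. This stands. It can change who is recruited, but it does not bias the treatment contrast on EPAS, and a reader should not infer that it does.

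**The failure is stipulated.** No passage reports a 3-point shift, and there are safeguards: trained raters, eligibility monitoring, and a descriptive check on the recruited population. This also stands, so the figures are an illustration and not a forecast. The safeguards do not supply the missing comparison.

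**A reader might infer that Spearman improves as over-rating grows**, because only patients who screen positive have a baseline assessment. If entry required HoNOS of at least 12, the coefficient would rise from about 0.61 to 0.69 at d = 3. The protocol does not support that reading: patients with HoNOS below 12 can enter through another scale plus a clinical recommendation. If 30%, 60% or 90% of them do (assumed), adding 3 points moves Spearman from 0.72 to 0.73, leaves it at 0.76, or leaves it at 0.78. Range restriction is real, but partial and of unknown degree.

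**A reader might equate the 79% with the share given an indication.** It is the share beyond one cut-off. The indication needs all three scales or a clinical recommendation.

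**The EPAS point is terminology.** Largely so: the administrator changes between occasions and relabelling alters no estimate. But the label attributes to raters a stability that belongs to the patient's own answers.

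**Conclusion.** The point holds as something that should be fixed. The protocol names a rank statistic as its only measure of agreement for a decision based on absolute scores. Its insensitivity to a uniform shift is a mathematical fact and needs no assumption. The size (ICC 0.80 to 0.68, and 58% to 79% at or above the HoNOS cut-off, for 3 points) rests on the assumed mean, SD, reliability and shift, in an unrestricted sample. The over-rating argument applies to HoNOS and CAN; EPAS is self-rated and is only mislabelled.

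What is at stake is the conclusion on whether the indication can be assessed reliably, not the randomised primary comparison.

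**What to change.** In Statistical methods {20a}, for HoNOS and CAN, replace or supplement Spearman with:
- a two-way, single-rater, absolute-agreement ICC with a confidence interval;
- the mean GBV-minus-research-worker difference with limits of agreement;
- percent agreement or kappa at each cut-off.

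Report the EPAS comparison as test-retest agreement.

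State the limits. Pairs exist only for patients given an indication, so false negatives at screening cannot be assessed. Agreement on the full three-level indication cannot be estimated either, because the no-indication category never reaches baseline. Part of any mean difference may be regression to the mean or true change between screening and baseline. With no over-rating, selection on HoNOS of at least 12 alone gave 0.5 to 1.0 points in the four scenarios of Step 3, and less when patients also enter through other scales.

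The cost is analysis wording only, using data already planned. Estimating agreement on the full indication would require double rating of some screen-negative patients, which is new data collection and not part of this request.

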### Outcomes {12}

All outcomes will be assessed over 24 months at 6-month intervals: *t*_0_, *t*_0_ + 6 months (*t*_1_), *t*_0_ + 12 months (*t*_2_), *t*_0_ + 18 months (*t*_3_), *t*_0_ + 24 months (*t*_4_).

The primary outcome is change in empowerment (EPAS, mean total score) [14] over 24 months. This outcome was chosen because contemporary care for people with permanent severe mental illness is aimed not only at controlling disease symptoms but also at empowering patients by increasing their capacities for a largely independent lifestyle and comprehensive social and professional inclusion.

The secondary outcomes include changes over 24 months in (1) satisfaction with psychiatric treatment using the Questionnaire of Treatment Satisfaction (ZuF8, sum score) [15, 16], (2) subjective quality of life using the World Health Organisation Quality of Life—short version (WHO-QoL-BREF, mean score rescaled to the range between 0 and 100) [17], (3) count of unmet needs for psychiatric and psychosocial services using the Camberwell Assessment of Need—European version (CAN) [18, 19], and (4) psychosocial and clinical impairment using the Health of the Nation Outcome Scale (HoNOS, sum score) [20–23]. Furthermore, the cost-utility of the GBV treatment in comparison to CAU will be investigated from the societal perspective and from the perspective of the statutory health insurance (payer perspective). Costs will be estimated from the view of the statutory health insurance and of the national economy using the Client Sociodemographic and Service Receipt Inventory (CSSRI) [24]. The cost-utility ratio is defined as the costs of gaining a “healthy” year of life (QALY), measured by the Euro Quality of Life—5 dimensions questionnaire (EQ-5D) [25].

The secondary outcomes assessed in informal caregivers will be changes over 24 months in (1) the perceived burden related to support of patient suffering from serious mental illness using the Involvement Evaluation Questionnaires (IEQ-EU, sum score) [26], (2) satisfaction with the patient’s psychiatric treatment using the ZuF8 (sum score) [15, 16], and (3) subjective quality of life using the WHO-QoL-BREF (mean score rescaled to the range between 0 and 100) [17].

The participants are asked to immediately report serious adverse events. Inpatient stays will be recorded at the next follow-up assessment, at the latest, by completing the CSSRI.

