### Sample size {14}

The calculation of the expected effect size is based on the results of a previous study (IVPOWER) [10]. Since the total score of the scale for measuring empowerment in patients with affective and schizophrenic disorders (EPAS) as the primary outcome proved to be rather difficult and slow to change, a low effect size of 0.20 and a high power of 0.90 were chosen for the sample size calculation of the present study.

The sample size calculation was based on a linear mixed-effects regression model with an interaction effect between study group and measurement time. The expected effect size, alpha value, beta value, number of measurements, number of study sites, and expected number of dropouts over all follow-up measurements were taken into account.

Based on the results of the IVPOWER study, an increase in the effect size of the primary outcome parameter is expected, from 0 standard deviations (SD) at baseline (*t*_0_) to 0.2 SD at the last assessment (*t*_4_). Furthermore, a decreasing dropout rate of 15% between *t*_0_ and *t*_1_, 7% between *t*_1_ and *t*_2_, 4% between *t*_2_ and *t*_3_, and 2% between t_3_ and t_4_ is expected, so that the expected sample size at *t*_4_ still comprises 72% of the initial sample.

A sample size calculation using the Web-based programme RMASS (www.rmass.org) yielded a number of at least 978 subjects for twelve study sites. On this basis, the target sample size was set at 1000 participants.

We expect to include about 350 informal caregivers, of whom about 225 will complete the study based on the experience gained in the IVPOWER study (recruitment rate = 36.8%; dropout rate = 35.6%).

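### The primary EPAS model is not said to share one t0 mean across arms; stating that constraint would gain precision from data already collected

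*Protocol article*

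**What the plan says.** Outcomes {12} states "The primary outcome is change in empowerment (EPAS, mean total score"), followed over 24 months, with assessments at t0 and every six months to t4. Statistical methods {20a} names the analysis: "The analyses of primary and secondary outcomes will follow the intention-to-treat (ITT) principle using mixed-effects models with random time effects", together with a time-by-treatment interaction. On the covariance it adds "The covariance structure will take the study sites and individuals into account". The section lists no treatment main effect, does not say that the t0 means are equal or unequal, and names no covariates.

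Sample size {14} uses the same kind of model: "The sample size calculation was based on a linear mixed-effects regression model with an interaction effect between study group and measurement time". It assumes a difference of 0 SD at t0 rising to 0.2 SD at t4, with 72% of participants left at t4, and arrives at 978, rounded up to 1000.

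Under Concealment mechanism {16b}, allocation is disclosed to the participant only once the baseline assessment is complete.

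EPAS, CAN and HoNOS are also taken at screening (Eligibility criteria {10}: "The following standardised scales will be applied as part of the assessment"). Their stated uses are eligibility and, in {20a}, agreement with the t0 ratings.

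**The concern.** By convention an interaction is fitted together with both main effects. On that reading each arm has its own t0 mean, and the treatment effect is divergence from arm-specific starting points, in effect a comparison of change scores. Randomisation makes the expected t0 means equal, and the sample size section itself starts from 0 SD. Estimating a t0 difference known to be zero in expectation carries its sampling error into the result.

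The simplest case shows why. With one baseline, one follow-up, equal variances and correlation ρ, the change-score comparison has variance proportional to 2(1−ρ) and the baseline-adjusted one 1−ρ². The ratio is (1+ρ)/2, or 0.775 at ρ=0.55.

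The target here is 0.2 SD on a scale that the protocol describes as slow to move, with 28% attrition, so precision is worth having.

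**Working it through.** **Inputs from the protocol.** Five assessments; 1:1 allocation; retention 1, 0.85, 0.78, 0.74, 0.72 (the stated dropout steps taken off additively, which gives the stated 72%); effect 0 at t0 and 0.2 SD at t4; from Sample size {14}, "a low effect size of 0.20 and a high power of 0.90 were chosen"; target N=1000.

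**Assumptions.** Alpha and the within-person covariance were inputs to the calculation ("The expected effect size, alpha value, beta value, number of measurements" heads the list), but the article does not print alpha or any correlation or variance component. I take alpha as two-sided 0.05, the effect as linear in time, and baseline SD as 1.

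**Formulas.** Let v be the generalised-least-squares variance of the t0-to-t4 treatment effect for one participant per arm, under monotone dropout. Then

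- required total N = 2(1.960+1.282)²·v/0.2² = 2×10.507×v/0.04
- power at N=1000 = Φ(0.2/√(2v/1000) − 1.960)

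Free model: intercept, time, treatment, time-by-treatment. Constrained model: the same without the treatment term.

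**Reproducing 978.** Comparing arms at t4 alone needs 1052 completers, or 1052/0.72 ≈ 1462 recruited, so that is not the source. The free linear model under compound symmetry (correlation 0.55) has v=1.8639, so N = 2×10.507×1.8639/0.04 ≈ 979, close to 978. AR(1) at 0.89 per six months gives 983. A constrained model with visit as a category also gives 978, at a compound-symmetry correlation of 0.54-0.56. The stated figure therefore does not reveal which model was intended.

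**Free against constrained, linear time-by-treatment effect.**

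| Assumed covariance | v free | v constrained | Ratio | N needed, free | Power at 1000, free → constrained |
|---|---|---|---|---|---|
| Compound symmetry 0.55 | 1.864 | 1.515 | 0.813 | 979 | 0.906 → 0.953 |
| AR(1) 0.89 | 1.871 | 1.589 | 0.849 | 983 | 0.905 → 0.944 |
| Intercept variance 0.6, slope SD 0.3 | 1.905 | 1.634 | 0.858 | 1001 | 0.900 → 0.938 |
| Intercept variance 0.7, slope SD 0.4 | 1.685 | 1.538 | 0.913 | 885 | 0.931 → 0.950 |
| Intercept variance 0.8, slope SD 0.5 | 1.505 | 1.441 | 0.958 | 791 | 0.954 → 0.961 |

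Slope SD is per 24 months; residual variance is 1 minus the intercept variance. The first two rows are those calibrated to about 978: variance falls by 19% and 15%. In extra participants, 1000×(1/0.813−1) ≈ 230 and 1000×(1/0.849−1) ≈ 178. The last row falls by 4%. A wider set of random-slope settings, not calibrated to 978, ran from about 3% to 25%.

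**Changing the test instead.** With visit as a category and only the t4 contrast tested, power at N=1000 goes from 0.840 to 0.902 under compound symmetry 0.55, and from 0.841 to 0.890 under intercept variance 0.6 with slope SD 0.3. The constraint helps there too, but the t4 contrast does not reach the power shown for the linear test.

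**Adding screening EPAS on top of the constraint.** With the correlation calibrated to 978, required N under compound symmetry falls from 796 to 665 (linear time) or from 841 to 723 (categorical). Under AR(1), with screening assumed one month before t0, it stays at 832.

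**The case against.** The strongest reply is that the document never says t0 is a free, arm-specific mean. A reader might infer that from the interaction term, but {20a} lists no treatment main effect, the listed terms also fit a constrained model, and 978 can be reached either way. Baseline handling and covariates are commonly left to the analysis plan, which the protocol refers to and which is not shown. This stands: the point is conditional on the usual fit, and no error in the document is established.

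A reader might also infer that the screening scores are ignored. They are not: they serve eligibility and the agreement analysis. All that can be said is that this article does not name them as covariates.

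A third tempting inference is that the planned analysis is biased or the trial underpowered. Under randomisation the free model is unbiased with valid type I error, and the calibrated cases give about 0.905 at N=1000.

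Finally, the constraint is not safe everywhere. The research worker requests randomisation around the time t0 is scheduled and hears back within one working day, so may hold the allocation before rating HoNOS and CAN. Caregivers return postal questionnaires, and the text does not place their t0 before disclosure. This also stands and limits the remedy. It bears less on EPAS, which participants complete themselves before they learn their allocation.

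**Conclusion.** The point holds as an efficiency improvement to the primary EPAS analysis. If the model is fitted with a treatment main effect, a common t0 mean lowers the variance of the linear time-by-treatment effect by about 4-19% in the cases tabulated, and by 15-19% where the assumed covariance gives about 978. Power at N=1000 in those calibrated cases moves from about 0.905 to 0.944-0.953. These sizes depend on two-sided alpha 0.05, a linear effect, the planned dropout and covariance structures that the article does not give; strong slope variation shrinks the gain towards the lower end. The documents do not support calling the planned analysis invalid or the stated power wrong. A benefit from screening EPAS is not secured: beyond the constraint it ranges from none under AR(1) to about 14-16% of N under compound symmetry (1−723/841 and 1−665/796), and the scores are range-restricted by the eligibility cut-off.

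**What to change.** State in the analysis plan that the primary EPAS model is a constrained longitudinal model: one t0 mean common to both arms, no treatment difference at t0, and the site and individual terms as planned. Keep the time-by-treatment test used for the sample size as the primary test; do not replace it with a single t4 contrast as a side effect of this change.

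For each secondary outcome, apply the constraint only if t0 is obtained without knowledge of allocation. For HoNOS and CAN, that means confirming that the research worker does not hold the allocation when rating t0. For caregiver outcomes, it means stating when their t0 is collected relative to disclosure. Otherwise leave the t0 difference free.

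Say whether screening EPAS enters as a covariate; either choice is defensible if fixed in advance. The change to the EPAS model costs wording before analysis and needs no new data.
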